## Demographic and Baseline Characteristics

The following demographic information will be listed and summarized for subjects in each treatment group: age, sex, medical history, smoking history, weak-up stroke, randomization time, NIHSS score, intravenous thrombolysis, occlusion site, ipsilateral carotid artery occlusion, ASPECT score, infarct core volume and stroke subtype.

The continuous data followed normal distribution will be presented as mean and standard deviation, and the continuous data followed skewed distribution will be presented as median and interquartile range; categorical data will be presented as n(%). T-test or Wilcoxon rank sum test will be used for comparison between continuous variables, and Chi-squared tests, Fisher's exact test or Wilcoxon sum rank test will be used for comparison between categorical variables.

## 12.Efficacy Analyses

### Primary Efficacy Analysis

The primary endpoint is the modified Ranking scale at 90-day. FAS will be the primary population for efficacy analyses. PPS will be used as secondary population for the efficacy analyses. If the results in the PPS population are inconsistent with the FAS population, detailed analysis of the inconsistent results is required.

#### Main Model

Based on an intention-to-treat basis, an ordinal logistic regression model with site as a random effect will be used to calculate the common odds ratio between the two treatment groups. If the proportional odds assumption for ordinal logistic regression were not satisfied, the Wilcoxon-Mann-Whitney generalized odds ratio will be calculated using assumption-free ordinal analysis. All statistics will be two-sided with  $p < 0.046$  considered significant.

---

## Interactions with Subgroups

Summary tables will be produced for the predefined subgroups and interactions between treatment and these subgroups will be investigated, using an ordinal logistic regression model. A separate model will be used for each interaction to determine its significance. This will also be presented graphically on a forest plot.

The predefined subgroups including:

- Age (< 75 vs. ≥75)
- Last known well to randomization time (< 6h vs. ≥ 6h)
- Stroke severity before randomization (NIHSS<16 vs. NIHSS≥16)
- Intravenous thrombolysis or not
- Occlusion site (ICA vs. M1 segment)
- ASPECT score (< 3 points vs. ≥3 points)
- Infarct core volume (< 70ml vs. ≥70ml)
- Etiological stroke subtype (cardiac embolism vs. large artery atherosclerosis)

## Secondary Efficacy Analyses

### 90-day mRS 0-2

The proportion of 90-day mRS 0-2 will be analyzed using a binary logistic regression model with site as a random effect. The odds ratio with 95% CI will be reported.

### 90-day mRS 0-3

The proportion of 90-day mRS 0-3 will be analyzed using a binary logistic regression model with site as a random effect. The odds ratio with 95% CI will be reported.

### 36h (24-48h) NIHSS 0-1 or decrease ≥10 from baseline

The proportion of 36h (24-48h) NIHSS 0-1 or decrease ≥10 points from baseline will be analyzed using a binary logistic regression model with site as a random effect. The odds ratio with 95% CI will be reported.

### 36h (24-48h) infarct volume change (by CT or MRI)

---

The change of 36h (24-48h) infarct volume change (by CT or MRI) will be analyzed using student t-test or Wilcoxon rank sum test as appropriate.

**36h (24-48h) target artery recanalization rate (by CTA or MRA)**

The 36h (24-48h) target artery recanalization rate (by CTA or MRA) will be analyzed using a logistic regression model with site as a random effect. The odds ratio with 95% CI will be reported.

## **13.Safety Analyses**

All analyses of safety data will be carried out using the safety set (SS) population.

**Primary Safety Endpoints**

Rate of symptomatic intracranial hemorrhage within 48 hours from randomization (Heidelberg Bleeding Classification).

**Secondary Safety Endpoints**

All-cause mortality within 90 days.

Rate of any intracranial hemorrhage within 48 hours from randomization (Heidelberg Bleeding Classification).

Rate of decompressive hemicraniectomy during hospitalization.

For most bleeding events, the binary logistic model with site as a random effect will be used to compare the odds ratio between the two treatments, or Poisson regression or negative binomial regression which are more appropriate for the analysis of rare event. For all-cause mortality within 90 days, the Cox proportional hazards model with site as a random effect will be used to compare the hazard ratio between the two treatments.

**Adverse Events**

Adverse events (AEs) will be coded using the MedDRA coding dictionary (Version 6.0 or a later release) and grouped by system organ class (as detailed in the study protocol). Separate data display listings and summaries will be presented for adverse events that start prior to first dose of study medication (pre-treatment), whilst on study medication

---

(during treatment) and after the last dose of study medication (post-treatment).

Within each treatment group, the number and percentage of subjects experiencing an AE will be summarized by system organ class and preferred term and Fisher's Exact test will be used to compare the number of each grouped AE event between treatment groups. In addition, a separate summary will be provided for AEs experienced by more than 5% of subjects in either of the treatment groups.

### **Serious Adverse Events**

Summary tables and data displays will be provided for serious adverse events (as detailed in the study protocol). In addition, all deaths and serious AE's will be documented in a case narrative format in the clinical study report.

The number of adverse events or serious adverse events occurring over the treatment period will be summarized and Fisher's Exact test will be used to compare between treatment groups.

## 1. Introduction

This statistical analysis plan (SAP) documents the planned statistical analyses for the ANGEL-ASPECT trial and is based on the protocol, together with any subsequent amendments.

This SAP is intended for the use of project team members and should be read in conjunction with the aforementioned protocol.

## 2. Study Objective

The primary objective of the study is to establish the efficacy of endovascular therapy (EVT) in Acute Anterior Circulation Large Vessel Occlusive (LVO) Patients with a large infarct core.

## 3. Study Endpoint(s)

Primary Efficacy Endpoints:

The 90 ( $\pm 7$ ) day modified Ranking scale.

Secondary Efficacy Endpoint:

- 1) 90 ( $\pm 7$ ) day mRS 0-2.
- 2) 90 ( $\pm 7$ ) day mRS 0-3.
- 3) 36h (24-48h) NIHSS 0-1 or decrease  $\geq 10$  from baseline.
- 4) 36h (24-48h) infarct volume change (by CT or MRI).
- 5) 36h (24-48h) target artery recanalization rate (by CTA or MRA).

---

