### **7.2 Secondary efficacy endpoint**

- (1) 90 days ( $\pm 7$  days) mRS 0-2
- (2) 90 days ( $\pm 7$  days) mRS 0-3
- (3) 36 hours ( $\pm 12$  hours) NIHSS 0-1 or decrease  $\geq 10$  from baseline
- (4) Infarct core volume change from baseline, at 7 days ( $\pm 1$  day) or at discharge assessed with NCCT or at 36 hours ( $\pm 12$  hours) assessed with MRI
- (5) 36 hours ( $\pm 12$  hours) target artery recanalization rate assessed with CTA or MRA

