### **(2) Efficacy Analysis**

Primary efficacy endpoint: Based on an ITT basis, an ordinal logistic regression model is used to calculate the common odds ratio between the two treatment groups. All statistics will be two-sided with  $p < 0.046$  considered significant.

Secondary Efficacy Analyses: Endpoints including the 90-day mRS 0-2 will be analyzed using a binary logistic regression model. The infarct core volume change from baseline will be analyzed using student t-test or Wilcoxon rank sum test as appropriate.

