The planned sample size is 502 cases, and two analyses will be conducted when the 90-day follow-up of 1/3 (168 cases) and 2/3 (336 cases) of the total sample size is completed, and the study may be terminated in advance based on clear validity or ineffectiveness. The expected duration of each subject's enrollment is approximately 1 year. Subjects will be followed with assessments at 36 (24-48) hours, hospital discharge (or  $7 \pm 1$  days),  $30 \pm 3$  days,  $90 \pm 7$  days and 12 months  $\pm 14$  days post randomization.

A blinded core laboratory will assess baseline imaging to confirm vessel occlusion

---

and determine ASPECT score, 36 (24-48) hours post-randomization to assess presence of ICH, and to measure core infarct volume and determine angiographical variables such as final reperfusion status and residual stenosis.

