### **36h (24-48h) infarct volume change (by CT or MRI)**

The change of 36h (24-48h) infarct volume change (by CT or MRI) will be analyzed using student t-test or Wilcoxon rank sum test as appropriate.

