### **36h (24-48h) target artery recanalization rate (by CTA or MRA)**

The 36h (24-48h) target artery recanalization rate (by CTA or MRA) will be analyzed using a logistic regression model with site as a random effect. The odds ratio with 95% CI will be reported.

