### 7.2 次要有效性评价指标

- (1) 随机化 90 (  $\pm 7$  ) 天 mRS 0-2 比例
- (2) 随机化 90 (  $\pm 7$  ) 天 mRS 0-3 比例
- (3) 随机化 36 (  $\pm 12$  ) 小时 NIHSS 0-1 分或较基线减少 $\geq 10$  分比例
- (4) 随机化 7 (  $\pm 1$  ) 天/出院 NCCT 或 36 (  $\pm 12$  ) 小时 MRI 评价的梗死体积较基线的变化
- (5) 随机化 36 (  $\pm 12$  ) 小时 CTA 或 MRA 判定的闭塞血管再通率

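### Infarct volume change (secondary efficacy endpoint 4) rests on a different scan in the protocol and the SAP for CT-followed patients, and its unadjusted test may forgo some precision

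*Supplement*

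**What the plan says.** **Protocol v7.1, section 7.2, item (4)** defines the endpoint as "Infarct core volume change from baseline, at 7 days" (±1 day) "or at discharge assessed with NCCT or at 36 hours" (±12 hours) with MRI. The synopsis and section 5.2(4) give the same rule. The Chinese protocol, section 7.2, pairs the same time points and modalities and also specifies change from baseline: "评价的梗死体积较基线的变化".

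**SAP v2.0, section 3** lists "36h (24-48h) infarct volume change (by CT or MRI"). Section 5 places the core-lab volume reading at the same visit: "36 (24-48) hours post-randomization to assess presence of ICH, and to measure core infarct volume". The analysis paragraph in section 12 repeats the 24-48 h window.

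**Test.** SAP section 12 says the endpoint "will be analyzed using student t-test or Wilcoxon rank sum test as appropriate". Protocol section 10.3.2(2) agrees: "The infarct core volume change from baseline will be analyzed using student t-test or Wilcoxon rank sum test as appropriate". The other four secondary efficacy endpoints in SAP section 12 are analysed with site as a random effect; the recanalization rate, for example, uses a "logistic regression model with site as a random effect".

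**The concern.** A 24-48 h CT and a day-7 or discharge CT are different measurements. They also have different evaluable patients, because anyone who dies between the two visits has only the earlier scan. The plan assumes 38% control mortality at 90 days but does not say how much of it falls before day 7, so the size of this difference is unknown. A reader holding both documents cannot tell which result is the pre-specified one.

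The second issue is the comparison itself. Baseline volume is the automated core from CT perfusion or from the ADC map (protocol 5.1(2)). Follow-up volume comes from non-contrast CT or MRI (5.2(4)). For CT-followed patients the change therefore subtracts across methods, and the planned test uses neither baseline volume nor baseline modality as a covariate. What is at stake is the meaning and precision of one secondary endpoint.

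**Working it through.** **1. The definitions side by side**

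| | Protocol v7.1 (7.2, 5.2(4), synopsis) | SAP v2.0 (3, 5, 12) |
|---|---|---|
| MRI route | 36 (±12) h | 24-48 h (same window) |
| CT route | Day 7 (±1) or discharge | 24-48 h |
| Reference | From baseline | Not stated |
| Rule if a patient has several scans | None | None |

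Nominal gap on the CT route: 7 × 24 − 36 = 132 h, or 5.5 days. Across the windows it runs from 144 − 48 = 96 h (4 days) to 192 − 24 = 168 h (7 days), and it is shorter after an early discharge.

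**2. Is it a deliberate change?** The SAP v2.0 revision table lists sample size, interim timing, boundaries and subgroups, but not this endpoint. SAP v1.0 has the same 24-48 h wording. Nothing in the documents records a decision to move away from the protocol.

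**3. Are both scans available?** Yes. Protocol 8.6 schedules CT+CTA or MRI with MRA at 36 h and a head CT for all enrolled cases at day 7 or discharge. The ischemic-volume row is marked at both visits, and footnote 5 gives the reading to the core lab from CT or MRI. An MRI-followed patient thus also has a day-7 CT, so the protocol's alternative leaves the choice of scan open within a patient.

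**4. Precision of the test.** The plan gives no SD, correlation, effect size or power for infarct volume, so there is no figure of its own to reproduce here. (Its only sizing, 452 evaluable patients for the ordinal mRS, does reproduce: the proportional-odds formula gives 450.3, or 452 with each arm rounded up. It has no bearing on this endpoint.)

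Let r be the baseline/follow-up correlation and k the follow-up SD divided by the baseline SD, with the baseline SD set to 1.

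- Change-score variance: 1 + k² − 2rk
- Baseline-adjusted variance: k²(1 − r²)
- Ratio: k²(1 − r²) / (1 + k² − 2rk)

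The proportional reduction equals (1 − rk)² / (1 + k² − 2rk). It is never negative, and it vanishes when rk = 1.

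| Assumed r | k = 1 | k = 1.5 | k = 2 |
|---|---|---|---|
| 0.3 | 0.65 | 0.87 | 0.96 |
| 0.5 | 0.75 | 0.96 | 1.00 |
| 0.7 | 0.85 | 1.00 | 0.93 |

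Example, r = 0.3 and k = 1: 0.91 / (2 − 0.6) = 0.65. Example, r = 0.3 and k = 2: 4 × 0.91 / (5 − 1.2) = 0.96.

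The reduction is therefore 15 to 35% with equal SDs and about 0 to 7% with a follow-up SD twice the baseline SD.

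**The case against.** **The SAP has already settled the time point.** Protocol 10.3 says the SAP will define the pre-specified analyses, and SAP sections 3, 5 and 12 consistently use 24-48 h. A reader might infer that the trial team is free to pick a time point after seeing the data. The documents do not go that far, since the SAP read alone fixes the window. What stands is that the SAP also describes itself as based on the protocol, the protocol names another CT scan as the endpoint, and neither says which prevails.

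**A 36 h CT volume has protocol support.** This is true of the schedule in 8.6, which marks a volume at both visits. It shows that the measurement is planned, not that it is the endpoint named in 7.2.

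**The test is sound.** It might be inferred that the test ignores baseline or is invalid. It does neither. A change score subtracts baseline, the Wilcoxon alternative is provided, protocol and SAP agree on the tests, and an unadjusted comparison of randomised arms is valid. A method offset common to both arms does not bias the difference between them. Footnote 2 of 8.6 also asks for the same imaging method at 24-48 h as at baseline, although that does not cover the day-7 CT.

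**The gain may be negligible.** This stands. Equal SDs are doubtful because two of the three imaging entry routes restrict baseline core to 70-100 ml, although the ASPECTS 3-5 route has no volume limit.

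**Adjusting for follow-up modality could introduce bias.** This also stands. Follow-up modality is settled after randomisation and may depend on treatment or on the patient's condition, so it does not belong in the main model.

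**Conclusion.** The definitional mismatch is certain: it is in the current text of both documents and affects every CT-followed patient. CT is the first-choice baseline work-up, so CT follow-up is probably common. The documents give no proportion, however, and calling it the majority would be a guess. They also contain nothing to show in which direction, or by how much, the two time points would differ.

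The analysis half is a matter of precision and interpretation, not of type I error. Its size depends wholly on an assumed r of 0.3 to 0.7 and on the SD ratio, so quoting 15 to 35% alone would show only the favourable case.

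This is one of five secondary efficacy endpoints. The primary analysis, the sample size and the stopping boundaries do not depend on it. It should be corrected, but it does not threaten the trial's main conclusion.

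**What to change.** Before database lock, and without sight of unblinded data:

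1. **One definition in both documents.** State the time point, the modality, *from baseline*, and a rule that selects one scan per patient when several exist. Which time point to use is for the sponsor to choose and justify. Report the other as supportive. Record the reconciliation in the revision tables.
2. **One adjusted comparison.** In SAP section 12 (and protocol 10.3.2), replace the unadjusted test with a linear model for change containing treatment, baseline core volume and baseline imaging modality, with site as a random effect as for the other secondary endpoints. The endpoint stays a change: with baseline volume in the model, the treatment effect is the same whether change or follow-up volume is the response.
3. **Follow-up modality** only in a sensitivity analysis. The present t-test or Wilcoxon test can be kept as a second one.

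The cost is wording. Both scans and the core-lab readings are already scheduled, and baseline volume and modality are already collected. Any change to the protocol text must go to the ethics committee under protocol 11.4.

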## Primary Safety Endpoint

- Rate of symptomatic intracranial hemorrhage within 48 hours from randomization (Heidelberg Bleeding Classification).

## Secondary Safety Endpoint

- 1) All-cause mortality within 90 days.
- 2) Any intracranial hemorrhage within 48 hours from randomization (Heidelberg Bleeding Classification).
- 3) Decompressive hemicraniectomy during hospitalization.

## 4. Statistical Hypotheses

The primary outcome will be a shift of one or more categories (proportional odds analysis) on the modified Rankin scale determined at 90 days from randomization.

The primary hypothesis is:

HA: Subjects in the group of best medical management plus EVT will have greater odds of showing improvement on the mRS at 90 days.

## 5. Design

This is a prospective, randomized, controlled, open label, blinded-endpoint (PROBE) study to compare the efficacy and safety of best medical management plus EVT compared to best medical management alone in Acute Anterior Circulation Large Vessel Occlusive (LVO) Patients with a large infarct core up to 24 hours from symptom onset or last seen well.

Patients who meet the inclusion criteria will be randomized to one of the following two treatment arms: best medical management plus EVT or best medical management alone. Endpoints in this prospective open label study will be assessed blinded to the

---

treatment assignment of the patient (PROBE design). This study will be conducted in approximately 50 sites in China.

**Best medical management plus EVT group:** Patients randomized to experimental group will receive EVT plus to best medical management. According to the pathological characteristics of patients and the judgment of researchers, the following treatment methods can be selected: Mechanical thrombectomy, angioplasty and arterial thrombolysis. Stent thrombectomy (Solitaire\*, EMBOTRAP#, Trevo or Reco and other first-line stent thrombectomy systems) and aspiration (Penumbra system) is recommended as the first choice. If the recanalization is not successful, it can be replaced with thrombus, balloon angioplasty or stent implantation. The need for rescue treatment is defined (including, but not limited to, a decision made by the investigator based on intraoperative conditions) as follows: three times of thrombectomy with the same thrombectomy device (stent or aspiration catheter) without successful recanalization; Target vessels were successfully recanalized and then occluded. Target vessel dissection or stenosis degree  $\geq 70\%$ , with any degree of forward flow disturbance; lumen/stent thrombus resulted in a decreased eTICI score.

**Best medical management group:** All the patients enrolled received standard guideline-directed medical therapy including: monitor vital signs, management of blood pressure, glucose and lipids, antithrombotic (antiplatelet or anticoagulant determined by treating physician) therapy if appropriate. Intravenous thrombolysis (IVT) will be performed before EVT for patients who were eligible in compliance with the existing guideline.

The planned sample size is 502 cases, and two analyses will be conducted when the 90-day follow-up of 1/3 (168 cases) and 2/3 (336 cases) of the total sample size is completed, and the study may be terminated in advance based on clear validity or ineffectiveness. The expected duration of each subject's enrollment is approximately 1 year. Subjects will be followed with assessments at 36 (24-48) hours, hospital discharge (or  $7 \pm 1$  days),  $30 \pm 3$  days,  $90 \pm 7$  days and 12 months  $\pm 14$  days post randomization.

A blinded core laboratory will assess baseline imaging to confirm vessel occlusion

---

and determine ASPECT score, 36 (24-48) hours post-randomization to assess presence of ICH, and to measure core infarct volume and determine angiographical variables such as final reperfusion status and residual stenosis.

## **6. Sample size estimates**

In this study, a multicenter, open, randomized, parallel control design method was used. The primary measure of efficacy was mRS score at 90±7 days after enrollment (considered as ordered variable). According to the literature data and clinical experts' opinions, the parameters were set as follows: (1) The proportion of mRS score 0-6 in control group was 3%, 4%, 10%, 17%, 16%, 12% and 38%, respectively; (2) The average treatment effect of EVT improved the outcome with the common OR value for improvement of mRS reached 1.73; (3) Two Interim analysis were considered. Adjusted level  $\alpha=0.046$  (two-sided) and power  $1-\beta=0.90$ . (4) The sample size was allocated to the intervention group and the control group in a 1:1 ratio. Based on these parameters, the total sample size was 452. Considering 10% attrition rate, the final total sample size was 502 cases, 251 cases in each group.

Interim analysis will take place when 1/3 (168 cases) and 2/3 (336 cases) have completed 3-month follow-up. O'Brien-Fleming boundaries will be used at the interim analysis as follows:

There are no established techniques for the assessment of interim trial efficacy boundaries using an ordinal logistic regression model (proportional odds model). Instead, we will revert to a simple dichotomous analysis of the mRS score at 0-2 defined at 90 days from randomization. The Z-statistic for this analysis shall be derived from the normal approximation of the binomial distribution as an unadjusted two-sample test of proportions. For an RCT comparing two treatment groups with respect to a binary outcome and two interim analysis, corresponding significance levels based on O'Brien & Fleming boundary are two-sided 0.0002 (stage 1), 0.0123 (stage 2) and 0.046 (stage 3, final analysis).

With the result of interim analysis, DSMB will make the decision to continue or

---

halt the study according to the test boundaries. The study will stop prematurely for futility if the result from the interim analysis indicate that we can't achieve an effective conclusion with the current sample size. Premature stopping for early success will be achieved if the interim analysis result has already proved the effect of intervention at significance level. Otherwise, the study will be continued until the predefined termination date. In interim analysis, the final sample size is allowed to be adjusted if the estimation of the primary outcome is drastically different from the actual data.

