## **10.4 Interim analysis**

Interim analysis will take place when 1/3 (168 cases) and 2/3 (336 cases) have completed 3-month follow-up. The O'Brien-Fleming boundaries will be used at the interim analysis as follows:

There are no established techniques for the assessment of interim trial efficacy boundaries using an ordinal logistic regression model (proportional odds model). Instead, we will revert to a simple dichotomous analysis of the mRS score at 0-2 defined at 90 days from randomization. The Z-statistic for this analysis shall be derived from the normal approximation of the binomial distribution as an unadjusted two-sample test of proportions. For an RCT comparing two treatment groups with respect to a binary outcome and two interim analysis, corresponding

significance levels based on the O'Brien & Fleming boundary are two-sided 0.0002 (stage 1), 0.0123 (stage 2) and 0.046 (stage 3, final analysis).

With the result of interim analysis, DSMB will make the decision to continue or halt the study according to the test boundaries. The study will stop prematurely for futility if the result from the interim analysis indicate that we can't achieve an effective conclusion with the current sample size. Premature stopping for early success will be achieved if the interim analysis result has already proved the effect of intervention at significance level. Otherwise, the study will be continued until the predefined termination date. In interim analysis, the final sample size is allowed to be adjusted if the estimation of the primary outcome is drastically different from the actual data.

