## 10.4 期中分析

期中分析将分别在完成首要终点访视的受试者数量达到总样本量的 1/3 ( 168 例 ) 和 2/3 ( 336 例 ) 时进行。多次检验将使用 O'Brien-Fleming 消耗函数法对检验水准进行调整, 对应的检验水准  $\alpha$  分别为双侧 0.0002 ( 第 1 次期中分析 )、0.0123 ( 第 2 次期中分析 )、0.046 ( 终末分析 )。

通过期中分析, 数据安全监查委员会 ( Data Safety Monitoring Board , DSMB ) 将决定研究继续或终止。针对研究失败的评估, 根据现有数据并结合预期最终样本量, 如本研究预期无法得出有效性结果, 将在当期即时终止研究。针对研究有效的评估, 如研究已经达到有效性标准, 并符合检验水准的要求, 可提前结束研究; 如评估疗效预期在研究结束时可达成, 则继续进行研究。如果研究中对主要结局的估计值与实际相差较大, 则最终样本量允许在期中分析时进行适当的调整。

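### Both interim looks test mRS 0-2 against levels that hold 5% only if one statistic is used throughout; if a crossing counts as success, overall error is about 5.4-5.5%, and early stopping for benefit is about half as likely as with the ordinal test

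*Supplement*

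**What the plan says.** The primary endpoint is the 90-day mRS as an ordered scale. SAP section 12 (Main Model) and protocol section 10.3.2 test it with an ordinal logistic model and a common odds ratio at two-sided p < 0.046. mRS 0-2 is listed as a secondary endpoint in SAP section 3 and protocol section 7.2.

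For the two looks, at 168 and 336 patients with 90-day data, protocol section 10.4 and SAP section 6 state: "There are no established techniques for the assessment of interim trial efficacy boundaries using an ordinal logistic regression model (proportional odds model". They continue: "Instead, we will revert to a simple dichotomous analysis of the mRS score at 0-2 defined at 90 days from randomization". The test is an unadjusted two-sample comparison of proportions. The levels 0.0002, 0.0123 and 0.046 are introduced as O'Brien-Fleming levels for a binary outcome with two interim analyses. SAP section 6 then lets the trial stop early for success once the interim result has shown the effect at its significance level.

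On futility, the same section says: "The study will stop prematurely for futility if the result from the interim analysis indicate that we can't achieve an effective conclusion". It names no statistic and no threshold.

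The Chinese protocol, section 10.4, gives the same levels and says only that O'Brien-Fleming spending adjusts them: "多次检验将使用 O'Brien-Fleming 消耗函数法对检验水准进行调整". It names no interim test statistic.

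**The concern.** A group-sequential set of levels is calibrated to the joint distribution of the statistics at the looks. Here the first two levels are spent on one statistic and the third on another. The two are only partly correlated, so the final test adds more new opportunity for a false positive than 0.046 allows for.

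Two further things are at stake. A trial stopped for success would have crossed on a secondary endpoint, with no stated role for the primary test at that point. And the looks would use a less sensitive statistic: it separates the 17% of controls expected to reach mRS 0-2 from the other 83% and ignores any shift within mRS 3-6.

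**Working it through.** **Inputs, all from SAP section 6.** Control arm: "The proportion of mRS score 0-6 in control group was 3%, 4%, 10%, 17%, 16%, 12% and 38%, respectively". Effect: "common OR value for improvement of mRS reached 1.73". Allocation 1:1. Two-sided α = 0.046, power 0.90. Evaluable number: "the total sample size was 452", and 502 with 10% attrition. Looks at 168 and 336. SAP section 9 has a general p < 0.05; I use the specific 0.046 of section 12, and 0.05 would raise the error further.

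1. **The plan's sample size.** Proportional-odds (Whitehead) formula: N = 12(z_α + z_β)² / [ln(OR)²(1 − Σp̄³)], with p̄ the mean of the two arms' category proportions. This gives 450.3, so 451 against the stated 452: reproduced within rounding.

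2. **The plan's levels.** O'Brien-Fleming-type spending at 168/502, 336/502 and 1 gives 0.0002, 0.0122 and 0.0462. The stated set is right for one statistic tested three times, and its overall two-sided error is then 0.0499.

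3. **Correlation of the two statistics under the null.** For a midrank score and a binary cut at proportion p, ρ = √[3p(1 − p)/(1 − Σp³)], where Σp³ runs over the seven categories. With p = 0.17, p(1 − p) = 0.1411 and Σp³ = 0.0667, so ρ = √(0.4233/0.9333) = 0.673. Using the pooled distribution of both arms instead gives 0.730.

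4. **Overall error as written, counting any crossing as success.** Trivariate normal with corr(Z₁, Z₂) = √(t₁/t₂) and corr(Zᵢ, Z₃) = ρ√tᵢ.

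| Case | Overall two-sided error |
|---|---|
| Same statistic throughout | 0.0499 |
| Mixed, ρ = 0.673 | 0.0547 (0.0273 in the direction of benefit) |
| Mixed, ρ = 0.730 | 0.0540 (0.0270) |
| Mixed, ρ = 0.9 | 0.0517 |
| Mixed, ρ = 0 (ceiling) | 0.0578 |

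   Simulation of multinomial mRS data (1,000,000 null trials) gives 0.0547 with final N 502 and 0.0540 with 452. The ordinal test at every look gives 0.0499 and 0.0486.

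5. **Final level needed if mRS 0-2 stays at the looks.** 0.0411 (ρ = 0.673) to 0.0417 (ρ = 0.730).

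6. **Chance of stopping early for benefit at OR 1.73.** Control odds of mRS 0-2 are 0.17/0.83 = 0.2048. Multiplied by 1.73 this is 0.3543, or 26.2% in the EVT arm.
   - mRS 0-2 at 336 patients: mean p = 0.2158, SE = √(0.2158 × 0.7842 × 2/168) = 0.0449, expected Z = 0.0916/0.0449 = 2.04.
   - Ordinal at 336: expected Z = ln(1.73) × √[336(1 − Σp̄³)/12] = 2.83.
   - Against a critical value of about 2.50 (p = 0.0123), the chances of crossing are 32% and 63%. Simulation of both looks together gives 32% and 62%.

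7. **Overall power at OR 1.73 (simulated).** Mixed plan: 92.9% at N 502 and 90.2% at N 452. Ordinal throughout: 92.9% and 90.1%.

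These figures leave out futility stopping (no numerical rule exists), the permitted sample-size change and the random site effect.

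**The case against.** The strongest reply is that the 5.4-5.5% treats an mRS 0-2 crossing as a rejection of the primary null. SAP section 12 still defines the primary analysis as the ordinal test at 0.046, and nothing expressly replaces it after a stop. If a success claim also needed ordinal p < 0.046 on the data at the stop, the overall error would be about 0.048 (0.0478 at N 502, 0.0475 at N 452). That arithmetic stands. But the plan does not state the requirement, and SAP section 6 ties success to the interim result itself. The excess is therefore conditional on that reading, and on any reading it is small.

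A second reply is that a harder early boundary is a defensible, cautious choice, since final power is intact. The power point stands: a reader might infer that the trial loses half its power, and it does not. The caution argument is weaker. Under the null the mRS 0-2 looks cross about as often as ordinal looks would (about 1.2% in each case), so the same error is spent for half the chance of stopping on a true effect.

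Two other inferences go too far. A reader might conclude that futility will be judged on mRS 0-2. The switch is introduced for efficacy boundaries, the futility sentence names no statistic, and the sample-size sentence after it refers to the primary outcome. A reader might also conclude that the Chinese text contradicts the SAP. It is silent on the interim statistic, and the protocol leaves the definition of planned analyses to the SAP.

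**Conclusion.** The point holds in limited form. The levels are correct for a single statistic and are applied to two. If an interim crossing counts as success, overall two-sided type I error is about 5.4-5.5% rather than 5.0%, or 2.7% rather than 2.5% in the direction of benefit. At OR 1.73, early stopping for benefit falls from about 62% to about 32%, with overall power unchanged. These figures rest on the plan's control distribution, proportional odds, and looks at 168 and 336 patients.

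The stated reason for the switch does not hold. The Wilcoxon or proportional-odds score statistic follows ordinary group-sequential theory, and with it the plan's levels give 0.049-0.050.

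This should be fixed before the first unblinded look, because it governs what a stop for success would mean. It does not invalidate the final primary analysis of a trial that runs to completion.

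**What to change.** In SAP section 6 and protocol section 10.4:

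- Delete the paragraph on the lack of established techniques. At each look, test the ordinal primary statistic (common odds ratio score or Wald test, or the equivalent Wilcoxon test) against 0.0002, 0.0123 and 0.046.
- Show mRS 0-2 to the DSMB as supportive information only.
- If mRS 0-2 is kept as the stopping statistic, either lower the final level to about 0.041 or state that a success claim after an early stop also requires the ordinal test.
- State that any futility assessment uses the ordinal primary statistic.
- Name the interim statistic in the Chinese section 10.4 so that both language versions give the DSMB the same rule.

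The cost is wording in the SAP, the protocol and, where it repeats the rule, the DSMB charter. The same 90-day mRS data are used. The preferred change adds no patients and leaves the planned levels and sample size as they are.
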